**MODIFICATION HISTOY:**

| Version(Date) | Authors | Action/modification |
| --- | --- | --- |
| V1 (2022-01-12) | [name], [name] | Created this statistical analysis plan (SAP) |
| V2 (2022-09-28) | [name], [name] | Revised SAP based on all coauthors' comments |
| V3 (2023-06-30) | [name], [name] | Revised SAP based on comments from external reviewers |

**STUDY OBJECTIVES**

To investigate the role of statin use on the risk of colorectal cancer (CRC), CRC-related mortality, and all-cause mortality in patients with inflammatory bowel disease (IBD).

**HYPOTHESIS**

Statin use is associated with lower risk of the development of CRC, CRC-related mortality, and all-cause mortality in patients with IBD.

**METHOD**

**Data source, study design, and study population**

This cohort study will be based on the nationwide histopathology cohort, Epidemiology Strengthened by histoPathology Reports in Sweden (ESPRESSO)^1^, and several healthcare registers in Sweden. ESPRESSO^1^ contains data on GI-related biopsies from all 28 pathology departments in Sweden from 1965 to 2017. The Total Population Register^2^ contains details on birth, death, and migration, which was initiated in 1968. The Prescribed Drug Register^3^ collects information on medications dispensed at all pharmacies in Sweden since July 2005, including for example dispensing date, drug name, and a defined daily dose (DDD). The National Patient Register^4^ covers data on inpatient (since 1964) and outpatient (since 2001) specialist care with disease diagnoses and surgical procedures. The Cancer Register^5^ contains data from >96% of incident cancer cases since 1958. The Cause of Death Register^6^ contains information on >99% of death since 1952. The Swedish Longitudinal Integrated Database for Health Insurance and Labour Market Studies^7^ contains information on demographic and socioeconomic characteristics (e.g., education and county of residence).

The IBD patients will be identified as those with ≥ 1 biopsy indicating IBD in the ESPRESSO and ≥ 1 International Classification of Disease (ICD) code for IBD in the NPR (see **Table 1** for the definition of IBD subtypes)^8^. Such diagnostic approach yields a positive predictive value of 95%^9^.

**Identification of statin users**

Statin use will be identified from the Prescribed Drug Register by the Anatomical Therapeutic Chemical (ATC) code C10AA, including lipophilic statins (simvastatin and atorvastatin) and hydrophilic statins (pravastatin and rosuvastatin) (see **Table 2** for ATC codes). Statin users will be identified as those aged ≥ 18 years and with a statin prescription for ≥30 cumulative DDD (cDDD) from July, 2006 or later. The date that an individual first attained a cDDD ≥ 30 for a statin will be defined as the index date for statin exposure. Individuals who had any statin prescription before July 2006, before IBD diagnosis or before the first attainment of cDDD ≥ 30 will be excluded from the analysis to ensure a new-user design. We will use the intention-to-treat analysis as the main analysis.

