**Two-step matching process**

A two-step matching process will be applied to establish the cohort. In the direct matching step, statin users and non-statin users will be matched on age at IBD diagnosis (<18, 18-<40, 40-<60, and ≥60), sex, IBD subtype (CD or UC), and calendar year at IBD diagnosis (1969-1989, 1990-1999, 2000-2009, 2010-2018). IBD-unclassified will not be considered in this project due to diagnostic uncertainty. To ensure similar opportunities for care and treatment^10^, non-statin users should have a random drug prescription (except IBD medications, see **Table 2** for ATC codes) within three months before or after the start date of statin treatment in the matched statin users. All identified non-statin users will be assigned the same index date as the index statin user. We will exclude individuals who had a record of migration, received a colectomy, or had a diagnosis of any of the following diseases before the index date: cancers, human immunodeficiency virus/ acquired immunodeficiency syndrome, primary immunodeficiency disease, end-stage renal disease, severe liver failure, and any organ transplantation (see **Table 2** for procedure and ICD codes).

In the propensity score matching step, statin users and non-statin users will be matched in a 1:1 ratio by using a greedy nearest-neighbor matching algorithm without replacement, with a caliper of 0.2 standard deviation of the logit of the propensity score^11^. A logistic regression model will be used to calculate the propensity score after adjusting for the below demographic and socioeconomic characteristics, comorbidities, and co-medications identified up to and including the index date.

- Age at IBD diagnosis, years (continuous);
- Duration of IBD, years (continuous);
- Number of healthcare visits (continuous);
- Country of birth (Nordic countries or others);
- Education (0-9, 10-12, ≥13 years, or missing);
- Comorbidities (yes/no, see Table 2 for detail): gastrointestinal diseases, intestinal infections, cardiovascular diseases, obesity/dyslipidemia, type 1 and type 2 diabetes, autoimmune diseases, obstructive sleep apnea, chronic obstructive pulmonary disease, and myositis;
- Medications (yes/no, see Table 2 for detail): antibiotics, proton pump inhibitor, antiviral medications, IBD medications, non-aspirin anti-platelet medications, aspirin, non-statin lipid lowering medications, anti-diabetic medications, anticoagulation medications, and anti-arrhythmias medications.

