**Secondary analyses**

Three secondary analyses will be conducted. First, to assess the relationship between continuous statin treatment and outcomes, we will apply an as-treated analysis where we further censor the follow-up at the end of the first treatment episode, in addition to the abovementioned censoring criteria. Second, to evaluate whether cumulative duration of statin use is associated with the outcomes, we will apply a nested case-control study in statin users. Using the method of incidence density sampling, for each case exposed to statin and with later studied outcomes, we will randomly select up to five statin users who did not develop the interested outcomes (controls). They will be individually matched on age at index date, gender, IBD subtype, IBD duration, and duration of follow-up. Conditional logistic regression will be used to estimate odds ratios (ORs) with 95% CIs. The cumulative duration of statin use will be assessed between first prescription and end of follow-up, and categorized into categories (30 days-<1 year (reference group), 1-<2 years, 2-<5 years, and ≥5 years cDDD). Trends in the dose-response association will be tested by using the duration strata as an independent variable in the model. Third, we will repeat the main analysis without accounting for competing risks.

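### The new-user exclusion conflicts with the cumulative definition of statin use: read literally, it keeps only people dispensed at least 30 DDD on their first statin date

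*SAP*

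**What the plan says.** The SAP, *Identification of statin users*, builds the exposed group in three steps.

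- **User.** An adult "with a statin prescription for ≥30 cumulative DDD (cDDD) from July, 2006 or later".
- **Index date.** "The date that an individual first attained a cDDD ≥ 30 for a statin will be defined as the index date for statin exposure".
- **Exclusion.** One sentence with three limbs. It begins "Individuals who had any statin prescription before July 2006" and continues "before IBD diagnosis or before the first attainment of cDDD ≥ 30 will be excluded from the analysis to ensure a new-user design".

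No section exempts the dispensings that themselves add up to 30 cDDD.

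Other sections use differently named dates. In *Two-step matching process*, a non-user needs another drug prescription "within three months before or after the start date of statin treatment in the matched statin users", but takes the matched user's index date. In the same section, the propensity-score model uses demographic characteristics, comorbidities and "co-medications identified up to and including the index date". In *Secondary analyses*, for the nested case-control study, "The cumulative duration of statin use will be assessed between first prescription and end of follow-up".

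**The concern.** The definition counts dispensings until they total 30 DDD, and the exclusion penalises having had any dispensing before that total is reached. A person who needs two dispensing dates to get to 30 meets the definition and fails the exclusion on the same facts.

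This rule sets exposure and time zero for the primary analysis, and two competent programmers could build different cohorts from it.

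- **Applied as written:** eligibility depends on the amount dispensed on the first day, and genuine new users who start with a smaller supply are lost.
- **With the third limb ignored:** those users stay, but their index date falls after treatment began. The covariate window then runs past treatment start, so visits, diagnoses or co-medications recorded after initiation can enter the propensity score.

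**Working it through.** The SAP gives no figure to reproduce here. The check is one of logic, with assumed dispensing sizes to exercise the rule.

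**Inputs from the SAP.** The threshold is 30 cDDD, and the index date is the first date on which it is reached. Any statin prescription before that date leads to exclusion. According to *Data source, study design, and study population*, the Prescribed Drug Register records dispensing date, drug name and DDD.

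**Assumption.** DDDs are credited on the day of dispensing.

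**Rule in symbols.** Let D1 be the first dispensing date and T the first date on which the running total is at least 30. The third limb excludes a person if any dispensing date is earlier than T. A person is therefore kept only if T = D1, that is, only if the DDDs dispensed on D1 total at least 30.

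**Equal dispensings every 90 days (sizes and spacing assumed).**

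| DDD per dispensing | Day 30 cDDD is reached | Outcome under the literal rule |
| --- | --- | --- |
| 5 | 450 | excluded |
| 10 | 180 | excluded |
| 15, 20, 28 or 29.9 | 90 | excluded |
| 30, 50, 90 or 100 | 0 | kept |
| two packs of 15 on day 0 | 0 | kept |

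**Random histories.** The rule was also applied to 200,000 simulated dispensing histories with assumed sizes and dates. Of these, 100,062 reached 30 cDDD after their first dispensing date, and none was kept. Nobody who reached it on the first date was excluded. The 100,062 reflects the assumed inputs and does not estimate the share of real users affected.

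**The other sections side by side.** Under the literal rule, treatment start, first prescription and index date are always the same day. With the limb ignored they can differ. The window for the non-user's prescription, the covariate window and the start of cumulative exposure may then be anchored on different days. The SAP does not say which case applies.

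**Size.** Let f be the share of otherwise eligible users whose first dispensing date totals less than 30 DDD. The SAP gives no dispensing sizes, so f can be anything from 0% to 100%. If events fall in proportion to users, the standard error of the log hazard ratio grows by the factor 1/√(1 − f). For illustration only:

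- f = 0.10: 1/√0.90 = 1.05
- f = 0.20: 1/√0.80 = 1.12
- f = 0.40: 1/√0.60 = 1.29

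These values of f are assumed, and nothing in the document favours one over another.

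**The case against.** The best defence is that the definition means one qualifying prescription of at least 30 DDD. The exclusion then removes people with an earlier, smaller prescription, follow-up starts at the first-ever dispensing, and the rule is strict but workable. It also makes treatment start and index date coincide, which suits the matching section. It is a possible reading, but it works only by leaving the words about accumulating and first attaining a total with nothing to do. The SAP does not state it.

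A second defence is that the limb was meant to catch statin use before the initiating episode. That is plausible as intent and worth preserving: without some such limb, a person with one 20-DDD fill in 2008 after IBD diagnosis who restarts in 2014 would count as new. But the text does not restrict the limb in that way.

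Three further objections stand and limit the point.

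- The literal reading makes the index date the first dispensing date, so it creates no post-initiation covariate window. Selecting on first-day supply affects precision and generalisability; no bias in the matched contrast has been shown.
- With the limb ignored, the gap between start and index is only the time taken to reach 30 DDD. It may be short, and many covariates are yes/no history items. The SAP does not allow the resulting distortion to be sized.
- The two harms are alternatives. One analysis cannot suffer both.

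**Conclusion.** The paragraph is internally inconsistent, and that conclusion needs no assumed figure. As written, the exclusion removes every new user who reaches 30 cDDD on a date after the first dispensing.

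The consequence is of unknown size. It is close to nil if first dispensings nearly always total 30 DDD or more, and larger if small first supplies are common.

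A reader might infer more than the document supports:

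- **That everyone who needs more than one pack is lost.** Several packs dispensed on the same day are not earlier than the attainment, so those people stay.
- **That the standard error is inflated by 5 to 29%.** That range rests wholly on an assumed f of 10 to 40% and on proportional loss of events.
- **That the hazard ratio is biased, or the baseline seriously contaminated.** The first has not been shown. The second is possible only if the limb is ignored, and its size is unknown.

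The point is worth correcting because it fixes who is exposed and when follow-up starts, not because a change in the result has been demonstrated.

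**What to change.** 1. Restate the third limb so that it excludes only people with a statin dispensing before the treatment episode in which 30 cDDD is first reached. Say expressly that the dispensings of that episode which add up to 30 cDDD do not count against the person. Define the episode; the as-treated analysis already relies on a first treatment episode, and one definition should serve both.
2. Keep the exclusions for any statin before July 2006 and before IBD diagnosis. Do not put a 12-month washout in their place, because it would admit people with an older sub-threshold fill and weaken the new-user design.
3. Keep the date of reaching 30 cDDD as the start of follow-up for both members of a pair.
4. Measure propensity-score covariates before the first statin dispensing of that episode, using the same calendar date for the matched non-user. The exclusion diagnoses and procedures can stay tied to the index date, applied alike to both members; the SAP should state that the two dates differ on purpose.
5. In *Two-step matching process* and *Secondary analyses*, replace the separate terms for treatment start and first prescription with whichever of these two dates is meant.

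The wording change is small, but cohort selection, matching and every dependent analysis must be re-run. This may be a real burden: the modification history and the list of non-prespecified analyses show that version 3 followed external reviewers' comments, so results may already exist. In that case, report how many users each reading keeps, so that the difference can be seen.

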**Two-step matching process**

A two-step matching process will be applied to establish the cohort. In the direct matching step, statin users and non-statin users will be matched on age at IBD diagnosis (<18, 18-<40, 40-<60, and ≥60), sex, IBD subtype (CD or UC), and calendar year at IBD diagnosis (1969-1989, 1990-1999, 2000-2009, 2010-2018). IBD-unclassified will not be considered in this project due to diagnostic uncertainty. To ensure similar opportunities for care and treatment^10^, non-statin users should have a random drug prescription (except IBD medications, see **Table 2** for ATC codes) within three months before or after the start date of statin treatment in the matched statin users. All identified non-statin users will be assigned the same index date as the index statin user. We will exclude individuals who had a record of migration, received a colectomy, or had a diagnosis of any of the following diseases before the index date: cancers, human immunodeficiency virus/ acquired immunodeficiency syndrome, primary immunodeficiency disease, end-stage renal disease, severe liver failure, and any organ transplantation (see **Table 2** for procedure and ICD codes).

In the propensity score matching step, statin users and non-statin users will be matched in a 1:1 ratio by using a greedy nearest-neighbor matching algorithm without replacement, with a caliper of 0.2 standard deviation of the logit of the propensity score^11^. A logistic regression model will be used to calculate the propensity score after adjusting for the below demographic and socioeconomic characteristics, comorbidities, and co-medications identified up to and including the index date.

- Age at IBD diagnosis, years (continuous);
- Duration of IBD, years (continuous);
- Number of healthcare visits (continuous);
- Country of birth (Nordic countries or others);
- Education (0-9, 10-12, ≥13 years, or missing);
- Comorbidities (yes/no, see Table 2 for detail): gastrointestinal diseases, intestinal infections, cardiovascular diseases, obesity/dyslipidemia, type 1 and type 2 diabetes, autoimmune diseases, obstructive sleep apnea, chronic obstructive pulmonary disease, and myositis;
- Medications (yes/no, see Table 2 for detail): antibiotics, proton pump inhibitor, antiviral medications, IBD medications, non-aspirin anti-platelet medications, aspirin, non-statin lipid lowering medications, anti-diabetic medications, anticoagulation medications, and anti-arrhythmias medications.

To examine if the matching has worked we will calculate standardized mean differences and comparing propensity score distribution and balance. A covariate with a standardized mean difference less than 10% will be considered well balanced.

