**Ethical approval**

This project will be conducted with ethical approvals from the Stockholm Ethics Review Board (2014/1287-31/4, 2018/972-32, and 2022-05774-02).

*Non-prespecified Analysis (Analysis according to comments from external reviewers):*

- Assess the association between statin use and risk of left-sided or right-sided colon cancer;
- Assess the association between statin use and cancer stage (measured by TNM classification and categorized into two groups: I-II or III-IV);
- To assess the robustness of our results, we added one sensitivity analysis by excluding individuals with a history of diabetes before statin initiation.

| Table 1. International Classification of Disease (ICD) codes and SNOMED codes for defining IBD | | | | | |
| --- | --- | --- | --- | --- | --- |
| IBD subtypes ^a^ | ICD-7 (1964-1968) | ICD-8 (1969-1986) | ICD-9 (1987-1996) | ICD-10 (1997-) | SNOMED codes ^b^ |
| Ulcerative colitis (UC) | 572,20; 572,21; 578,03 | 563,1; 563,10; 569,02; 569,04 | 556 | K51 | D6255 or M41, M42, M43, M44, M463, or M47 |
| Crohn's disease (CD) | 572,00; 572,09 | 563,00 | 555 | K50 | D6216 or M41, M42, M43, M44, M463, or M47 |
| IBD unclassified (IBD-U) | UC + CD | UC + CD or 563; 563,0; 563,9; 563,98; 563,99 | UC + CD | UC + CD or K52.3 | D6214 or M41, M42, M43, M44, M463, or M47 |
| ^a^ Subtypes of IBD were defined according to the first two diagnostic codes only, therefore no information after start of follow-up contributed to such definition; and the IBD subtype was only determined by the ICD code if one individual had one ICD code for IBD and one M code. ≥1 ICD code for IBD plus a relevant biopsy code has a positive predictive value of 95% ^9,16^. In a recent paper ^17^, we report that 18% of incident IBD patients in the Swedish patient register during 2002-2014 were classified as another IBD subtype at some point during follow-up. | | | | | |
| ^b^ SNOMED codes starting with M (inflammation suggestive of IBD, but not a specified subtype) were required to be accompanied by a topographic code of T67 or T68 (colon); for example, M41 refers to all codes starting with M41; D codes are diagnostic codes but listed under morphology in pathology registers; D6255, for example, is the diagnostic code for UC. | | | | | |

| Table 2. Definitions of statin, outcomes, exclusion criteria, comorbidities, and medications | |
| --- | --- |
| Statin | **ATC code** ^a^ |
| Simvastatin | C10AA01 |
| Pravastatin | C10AA03 |
| Atorvastatin | C10AA05 |

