| Rosuvastatin | C10AA07 |
| **Outcomes** | **ICD code** ^a^ |
| Incident colorectal cancer (CRC) ^b^ | ICD-7: 153-154, but not 1541 (anal cancer) or 1534 (appendiceal cancer) |
| CRC-related mortality | ICD-10: C18-20, but not C181 (appendiceal cancer) |
| All-cause mortality | ICD-10: A00-U99 |
| **Proctocolectomy and colectomy** | **Procedure code** |
| Proctocolectomy ^c^ |  |
|  | Sixth version (1969-1996): 4652, 4653, 4654 |
|  | Seventh version (1997-): JFH20-JFH40 |
| Colectomy with an intact rectum ^d^ |  |
|  | Sixth version (1969-1996): 4650, 4651 |
|  | Seventh version (1997-): JFH00, JFH01, JFH10, JFH11, JFH96 |
| Rectum amputation after a colectomy with an intact rectum ^e^ |  |
|  | Sixth version (1969-1996): 4820, 4821, 4822, 4828 |
|  | Seventh version (1997-): JGB00-JGB97 |
| **Exclusion criteria** | **ICD-10 code/procedure code** |
| Cancer | C00-C97, except non-melanoma skin cancer (C44) |
| HIV/AIDS | B20-B24, F024, O987, R75, Z114, Z219, Z711 |
| Primary immunodeficiency disease | D71, D80–D84 |
| Severe liver failure | B150, B160, B162, B190, K704, K72, K766, I85 |
| End-stage renal disease | N18.5,  N18.6, Z49, Z99.2, Z94.0; Procedure codes: 9200; V9200; 9212; V9212; 9314; V9531; DR012; DR013; DR016; DR024; QF006; 9211; V9211; 9213; V9213; V9532; DR015; DR023; DR055; DV056; 9219; V9219; 9223; V9223; DR017; DR020; DR055; DR056; 6070; KAS10; KAS20 |
| Any organ transplantation | Swedish surgery codes (KVÅ codes): KAS, FQA, FQB, GDG, JJC |
| **Comorbidities** | **ICD-10 code** |
| Gastrointestinal diseases | K00-K99 |
| Intestinal infections | A00-A09 |
| Cardiovascular diseases | I00-I99 |
| Obesity/dyslipidemia | E78 , E65, E66 |
| Type 1 and type 2 diabetes | E10-E14 , O24 |
| Autoimmune diseases | E035, E039, E050, E055, E059, E063, E065, G35, M05-M09, M32, L40 |
| Obstructive sleep apnea | G473 |
| Chronic obstructive pulmonary disease (only if diagnosed ≥40 years) | J41-J44 |
| Myositis (no adequate codes present for rhabdomyolysis) | M60 |
| **Medications** | **ATC code** |
| Antibiotics | J01 |
| Proton pump inhibitor | A02BC |
| Antiviral drugs | J05 |
| IBD medications |  |
| Immunomodulators |  |
| Azathioprine | L04AX01 |
| Mercaptopurine | L01BB02 |
| Methotrexate | L04AX03/L01BA01 |
| Anti-TNF treatment |  |
| Infliximab | L04AB02 (L04AA12 before 2008) |
| Adalimumab | L04AB04 (L04AA17 before 2008) |
| Golimumab | L04AB06 |
| Vedolizumab | L04AA33 |
| Systemic corticosteroids |  |
| Betamethasone | H02AB01 |

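### Disease extent and sclerosing cholangitis are not covariates in either matching step, so the colorectal cancer hazard ratio may be confounded by disease phenotype and the balance check cannot show it

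*SAP*

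**What the plan says.** The SAP section *Two-step matching process* sets the covariates out in full. Direct matching uses age band at IBD diagnosis, "sex, IBD subtype (CD or UC), and calendar year at IBD diagnosis". The propensity score then adds age at diagnosis, IBD duration ("Duration of IBD, years (continuous"), healthcare visits, country of birth, education, a set of yes/no comorbidities and a set of yes/no medications. The comorbidity item begins "Comorbidities (yes/no, see Table 2 for detail): gastrointestinal diseases, intestinal infections, cardiovascular diseases, obesity/dyslipidemia".

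The tables define the terms:

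- **Subtype (Table 1).** For ICD-9 and ICD-10, ulcerative colitis and Crohn's disease are whole three-character codes. The ulcerative colitis row reads "556 | K51 | D6255 or M41, M42, M43, M44, M463, or M47".
- **Gastrointestinal comorbidity (Table 2).** "Gastrointestinal diseases | K00-K99".
- **Autoimmune comorbidity (Table 2).** "E035, E039, E050, E055, E059, E063, E065, G35, M05-M09, M32, L40", with no hepatobiliary code.
- **Severe liver failure exclusion (Table 2).** "B150, B160, B162, B190, K704, K72, K766, I85".

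Every cohort member must also have "≥ 1 International Classification of Disease (ICD) code for IBD in the NPR". Balance is judged by a standardized mean difference below 10%. E-values and a fracture negative control are planned as sensitivity analyses.

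**The concern.** The primary outcome is incident CRC. How much of the colon is inflamed, and whether the patient has sclerosing cholangitis, are disease features that a reader in this field would expect to bear on that outcome. This is subject-matter knowledge; the SAP does not state it. The SAP does accept the related principle that the amount of bowel at risk matters: after a colectomy that spares the rectum, a patient is followed for rectal cancer only.

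As specified, a matched pair agrees on Crohn's disease or ulcerative colitis but may differ in extent, in location or in cholangitis. If those features also relate to starting a statin, given everything else in the score, the CRC hazard ratio absorbs the difference. Because the features are not in the covariate list, they will not be in the balance table either, and a table with every item under 10% would give no warning.

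**Working it through.** The SAP states no figure on this point, so there is nothing of its own to reproduce. The check has two parts.

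**1. Is either feature covered under another name?**

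- *Extent or location:* no such item appears in the direct match, the score, Table 1 or Table 2. The subgroup list has subtype and duration but not extent.
- *Sclerosing cholangitis:* it is not named anywhere. The autoimmune codes contain no hepatobiliary entry, and the liver exclusion covers severe failure only.
- *The K00-K99 flag:* this is the only covariate that could contain a cholangitis code. K50 and K51 lie inside the same range, every member needs an IBD code, and the SAP does not remove K50/K51 from the flag. It is therefore positive for practically everyone. Even with K50/K51 removed, it would merge cholangitis with all other digestive disease.

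**2. How large could the bias be?** For a binary risk factor with prevalence p1 in users, p0 in non-users and CRC rate ratio RR, and with no true statin effect:

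spurious ratio = [1 + p1(RR − 1)] / [1 + p0(RR − 1)]

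SMD = (p1 − p0) / √{[p1(1 − p1) + p0(1 − p0)] / 2}

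The first formula is a rate-ratio approximation to what would happen to the SAP's subdistribution hazard ratio. All values of p and RR are assumptions; none comes from the documents.

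| Factor | p1 | p0 | RR | Spurious ratio |
|---|---|---|---|---|
| Cholangitis | 0.02 | 0.03 | 2 | 1.02/1.03 = 0.99 |
| Cholangitis | 0.02 | 0.04 | 4 | 1.06/1.12 = 0.946 |
| Cholangitis | 0.02 | 0.05 | 5 | 1.08/1.20 = 0.90 |
| Extensive disease | 0.40 | 0.50 | 2 | 1.4/1.5 = 0.93 |
| Extensive disease | 0.40 | 0.50 | 3 | 1.8/2.0 = 0.90 |
| Extensive disease | 0.40 | 0.50 | 4 | 2.2/2.5 = 0.88 |
| Extensive disease, reversed | 0.50 | 0.40 | 2 | 1.5/1.4 = 1.07 |
| Extensive disease, reversed | 0.50 | 0.40 | 4 | 2.5/2.2 = 1.14 |

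Absolute SMDs, had the features been measured:

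- 2% vs 3%: 0.01/√0.02435 = 0.064
- 2% vs 4%: 0.02/√0.029 = 0.117
- 40% vs 50%: 0.10/√0.245 = 0.202

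The last two would fail the SAP's 10% criterion; the first would pass it. Under the current covariate list none would be seen.

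The range depends heavily on the assumptions. Cholangitis at 1-2% vs 3-4% with RR 2-10 gives 0.99 to 0.80. Extensive disease at 25-35% vs 40% with RR 1.5-5 gives 0.98 to 0.77.

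**The case against.** The strongest case against is that a risk factor confounds only if it is also related to statin initiation after matching, and the SAP shows no such link for either feature. That stands. A reader might infer that the main hazard ratio *is* confounded, or that the bias would imitate protection. The documents support neither reading. For extent there is no stated reason to expect one direction over the other, and for cholangitis any reluctance to prescribe statins would be outside knowledge.

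A second line is that partial control exists, and this also stands in part:

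- A reader might take IBD treatment to be a single drug flag. Table 2 lists immunomodulators, anti-TNF treatment, systemic steroids, systemic and rectal aminosalicylates and local steroids under that item, and the text does not say that they are collapsed into one.
- A reader might take ileal-only and colonic Crohn's disease to be wholly interchangeable. Table 1, footnote b, requires a colon topography code for M-coded biopsies, so the gap lies with patients who enter through the subtype-specific D code.
- Duration, healthcare visits, and the exclusions for prior colectomy, transplantation and severe liver failure remove or track some advanced disease.

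These are proxies. None separates limited from extensive colitis or identifies cholangitis short of liver failure. E-values ask how strong an omitted factor would have to be, and the fracture outcome does not target bowel phenotype. Both gauge residual confounding without reducing it.

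Third, the usability of extent subcodes in the registers is not shown in the documents, and IBD diagnoses go back to 1969 while ICD-10 starts in 1997. This is a fair limit on the remedy for extent.

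**Conclusion.** The point holds as a possibility that the plan leaves open. Two plausible baseline determinants of the primary outcome are missing from a closed covariate list, the broad gastrointestinal flag cannot stand in for them, and the planned diagnostics cannot detect an imbalance in them. Size and direction are unknown from the documents. Under the main assumed scenarios the spurious ratio is 0.99-0.90 for cholangitis and 0.93-0.88 for extensive disease, or 1.07-1.14 if the extent imbalance is reversed. This rests on three assumptions: that the features affect CRC risk, that they relate to statin start given the existing covariates, and that the prevalences and rate ratios are of the order shown. It does not establish that the result is biased. It is a gap worth closing because closing it is cheap.

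**What to change.** 1. Define sclerosing cholangitis before or at the index date as its own yes/no covariate, with its codes listed in Table 2. Enter it in the propensity score and the balance table.
2. Repeat the CRC analysis without patients who have that flag.
3. Define disease extent or location at index from register subcodes and histology topography, with a separate unspecified category. Add it to the score and balance table if the codes prove usable.
4. If they do not, report a quantitative bias analysis for extent, with stated prevalences and rate ratios, and name the limitation.

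The cost is SAP wording, a re-run of the match and the analyses that follow from it, some misclassified or unspecified extent, and possibly slightly fewer matched pairs. The diagnosis and histology registers are already linked, so no new data source is needed.
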